### Participant timeline {13}

Timeline VeSpAR trial is shown in Fig. 1.

**Fig. 1 Fig1:**
[figure not shown]
Timeline VeSpAR trial. VCUG, voiding cysto-urethrography

### Sample size {14}

Power analysis and sample size calculation for this non-inferiority trial were performed using an online software package:

Sealed Envelope Ltd. 2012. Power calculator for binary outcome non-inferiority trial. [Online] Available from: https://www.sealedenvelope.com/power/binary-noninferior/ [Accessed Mon Apr 162,018].

Different scenarios were simulated, of which the results are discussed below. In all scenarios, 10% was considered the non-inferiority limit, *d*, as mentioned above.

- Scenario 1: power 0.80; estimated success in control group (tAR): 95.4%; estimated success in experimental group (vsAR): 95.3%; for different one-sided alphas:

❖ Alpha 0.025: 72 patients per arm

❖ Alpha 0.05: 56 patients per arm

❖ Alpha 0.10: 41 patients per arm

- Scenario 2: power 0.80; estimated success in control group (tAR): 95.4%; estimated success in experimental group (vsAR): 95.4%; for different one-sided alphas:

❖ Alpha 0.025: 69 patients per arm

❖ Alpha 0.05: 55 patients per arm

❖ Alpha 0.10: 40 patients per arm

- Scenario 3: power 0.80; estimated success in control group (tAR): 97.4%; estimated success in experimental group (vsAR): 93%; for different one-sided alphas:

❖ Alpha 0.025: 227 patients per arm

❖ Alpha 0.05: 179 patients per arm

❖ Alpha 0.10: 131 patients per arm

The numbers that were put in the above simulations are based on an in-home analysis of patients who underwent anastomotic repair at Ghent University Hospital between 2000 and 2017. Herein the FFS at 24 months for vsAR and tAR were 95.3% (standard deviation (SD), 2.3%) and 95.4% (SD, 2.0%) respectively. These exact results are represented in scenario 1. Scenario 2 represents a situation in which the surgical outcome would be exactly the same for vsAR and tAR. Scenario 3 represents a less favorable situation in which vsAR has a 24 m-FFS of 93% (95.3% − SD) and tAR has a 24 m-FFS of 97.4 (95.4% + SD).

In every scenario, the power was set at 0.80, according to the guidelines for designing a phase II trial [21]. The results for different alphas are displayed above. Usually, a non-inferiority trial demands a significance level, alpha, of 0.025 as these trials only look at one boundary of the classic two-sided 95% confidence interval (CI) [22]. However, these conditions often lead to (sometimes unreasonably) high sample size calculations requiring excessive financing and recruitment. As a solution, researchers often design a phase II trial that allows for more coincidence and thus a trial with a higher significance level, alpha. Rubinstein et al. reported alpha values of 0.10 and 0.20 to be allowed in a phase II trial [21]. Considering the fact that a non-inferiority trial relies on one-sided testing, we believe a one-sided significance level, alpha, of 0.10 is allowed and most feasible.

Considering all of the above, a scenario in which the power is set at 0.80, the one-sided significance level, alpha, is set at 0.10, the estimated success in control group is set at 95.4%, and the estimated success in experimental group is set at 95.3% was found most realistic and feasible. Considering this and accounting for a realistic drop-out of 20% (experience based), it was estimated that each arm has to consist of 50 patients, resulting in a total sample size of 100 patients.

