**Methods:**

This trial is a prospective, interventional, multi-center, single-blinded, 1:1 randomized, controlled, non-inferiority, phase II trial. Sample size calculation resulted in a required sample size of 100 patients (50 patients per arm). Trial participants will be randomized by an independent third party using a computer-based random sequence generator with permuted blocks of variable size. The primary objective of this trial is to show that vsAR is non-inferior to tAR in terms of failure-free survival after 24 months of follow-up, considering a non-inferiority limit of 10%. Failure is defined as the inability to pass a 16-Fr flexible cystoscope through the reconstructed area without damaging the urethral mucosa. Secondary end-points mainly include differences in postoperative complications and changes in functional outcome parameters, which will be assessed with validated questionnaires. All participants are scheduled for follow-up at 3, 12, and 24 months postoperatively.

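### The 20% drop-out allowance is slightly short: 41 evaluable men per arm requires 52 randomised per arm, not 50, and the nominal power is 79.4% instead of 80%

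*Protocol article*

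**What the plan says.** All inputs are in the protocol article, section Sample size {14}. On the margin: "In all scenarios, 10% was considered the non-inferiority limit". On power: "In every scenario, the power was set at 0.80". For the scenario finally adopted, "the one-sided significance level, alpha, is set at 0.10", "the estimated success in control group is set at 95.4" (per cent), and "the estimated success in experimental group is set at 95.3% was found most realistic and feasible". These are the inputs of scenario 1, for which the same section lists "Alpha 0.10: 41 patients per arm".

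The section then moves from the evaluable number to the number to be randomised: "accounting for a realistic drop-out of 20% (experience based), it was estimated that each arm has to consist of 50 patients". It does not say how the allowance was calculated. The Methods part of the abstract repeats the result, 100 patients in total, as the required sample size.

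Two other sections bear on the size of the effect. Section {20c} censors men who drop out at their last follow-up. The section on analysis of the primary end-point compares 24-month failure-free survival using Kaplan-Meier estimates and an 80% confidence interval for the difference.

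**The concern.** A drop-out allowance should return the required number once the expected loss has occurred. Here it does not: removing 20% of 50 leaves 40, and the protocol's own calculation asks for 41. The planned size therefore does not follow from the inputs given for it.

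What is at stake is mainly the accuracy of the stated design. The protocol presents 100 patients as the number that gives 80% power after 20% drop-out, and the trial report will probably repeat this. If the result falls just short of non-inferiority, readers will judge it against that stated power.

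**Working it through.** **Inputs** (Sample size {14}): control success 0.954; experimental success 0.953; margin 0.10; one-sided alpha 0.10 (z = 1.2816); power 0.80 (z = 0.8416); drop-out 20%. Allocation is 1:1 (Trial design {8}).

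**Step 1. Reproduce the protocol's 41.** Binary non-inferiority formula with unpooled variance:

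n = (z_alpha + z_beta)² × [p_c(1 - p_c) + p_t(1 - p_t)] / [margin - (p_c - p_t)]²

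- Variance term: 0.954 × 0.046 + 0.953 × 0.047 = 0.043884 + 0.044791 = 0.088675
- Denominator: (0.10 - 0.001)² = 0.099² = 0.009801
- n = (2.1232)² × 0.088675 / 0.009801 = 40.79, rounded up to **41**

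This agrees exactly with the listed figure. The same formula reproduces eight of the nine sample sizes in the section. The ninth (scenario 3, alpha 0.10) comes out at 130 against a stated 131, which does not affect this point.

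**Step 2. Apply the drop-out allowance.**

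- From the rounded number: 41 / (1 - 0.20) = 51.25, so **52 per arm, 104 in total**
- From the unrounded number: 40.79 / 0.80 = 50.98, so 51 per arm, 102 in total
- Stated: 50 per arm, 100 in total

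The shortfall is one or two men per arm, depending on where the rounding is done.

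**Step 3. Check in the other direction.** 50 × 0.80 = 40 evaluable per arm, one below 41. To keep 41 out of 50, drop-out can be at most 1 - 41/50 = 18%.

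**Step 4. Power under the same formula.**

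Power = Phi( 0.099 / sqrt(0.088675 / n) - 1.2816 )

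| Evaluable per arm | Power |
|---|---|
| 40 (50 less 20%) | Phi(2.103 - 1.282) = **79.4%** |
| 41 (stated requirement) | 80.2% |
| 41.6 (52 less 20%) | 80.6% |
| 50 (no loss) | 85.8% |

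The gap to the nominal 80% is 0.6 percentage points.

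**Step 5. Where 50 may have come from.** Two calculations give it: 41 × 1.2 = 49.2, rounded up to 50; or scenario 2 (95.4% in both arms), which lists 40 per arm, and 40 / 0.80 = 50. The protocol does not say which was used, or whether 50 is simply a round number. The mismatch does not depend on the answer.

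**The case against.** The strongest reply is that the difference has no practical weight. It is one or two men per arm and 0.6 points of power, and the 20% is itself an estimate from experience; at 18% drop-out the requirement is met. This stands as an argument about importance. It does not make the two figures agree.

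A second reply is that men who drop out are not lost to the analysis. They are censored at last follow-up, so a man seen at 3 or 12 months still adds information. This also stands. At 20% loss, 10 of 50 men per arm drop out, and if those ten together contribute as much as one fully followed man, the effective number is 41 and the formula gives 80.2%. The 79.4% is therefore a lower bound under that formula, with the true position between 40 and 50 per arm.

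A third reply is that 50 is exactly right for scenario 2. But the text adopts 95.3% for the vessel-sparing arm, which is scenario 1. If scenario 2 was used, the stated basis needs correcting instead.

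A reader might go further and infer that the trial misses its 80% power in any material sense. The documents do not support that, for the reasons just given. A reader might also attach lower power figures obtained from exact calculations with other confidence limits. Those figures reflect the choice of interval when few failures are expected, and do not come from the drop-out step: a Newcombe limit, for instance, gives 72.6% at 40 per arm and 72.0% at 41, so adding the missing man would not raise it. Nor can it be said as fact that the authors multiplied by 1.2, since no formula is given.

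**Conclusion.** Wrong as written, and minor. With 41 evaluable men per arm and 20% drop-out, the required number is 52 per arm (51 from the unrounded calculation). The stated 50 leaves 40, one short. Nominal power at 40 is 79.4% by the formula that reproduces the protocol's own figure.

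This rests on three assumptions: the scenario 1 success rates; a 20% loss that covers every man who does not complete follow-up, including any excluded after a change to another technique; and, for the 79.4%, treating each drop-out as contributing nothing. The last is stricter than the planned analysis, and with non-informative censoring the real loss of power from drop-out should be no larger.

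**What to change.** Either of two changes settles it:

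1. Correct the sample size to 41/0.80 = 52 per arm, 104 in total, in the sample size section and the abstract. The cost is four more patients.
2. Keep 100 patients and add a sentence saying that 20% drop-out leaves 40 evaluable per arm, for which the formula gives a nominal power of about 79%, and that censored men still contribute to the Kaplan-Meier estimate. The cost is one sentence and no extra patients.

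In both cases, state the inflation formula, and confirm that scenario 1 is the basis. No change to the design or the primary analysis is needed.

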### Recruitment {15}

All patients meeting the inclusion criteria of the trial and presenting at one of the participating centers will be informed about the trial and will be asked to participate (Fig. 2).

**Fig. 2 Fig2:**
[figure not shown]
SPIRIT figure for enrolment, interventions, and assessments. vsAR, vessel-sparing anastomotic repair; tAR, transecting anastomotic repair; VCUG, voiding cysto-urethrography

Strategies for achieving adequate participant enrolment in this trial include:
Repetitive review of the recruitment status (overall and per participating center) every 3 months.Informing local PIs about their recruitment status and how this relates to other study sites.

The recruitment period is estimated to end in January 2021.

## Assignment of interventions: allocation

### Sequence generation {16a}

Random allocation of patients to one of both treatment arms will occur through a computer-based random sequence generator with permuted blocks of variable size. Randomization will be stratified by participating center.

### Concealment mechanism {16b}

Random allocation of patients to one of both treatment arms will be done by a third party who is further not involved in any process of the trial. When a participating center other than Ghent University Hospital wants to allocate a patient to one of both treatment arms, the local PI will contact the third party for randomization within 1 week before the planned operation (by central telephone number or e-mail address) and will ask to which treatment arm “patient X who is going to be operated on dd/mm/yyyy” is allocated. Note that there will be no communication of names, initials, or birth dates of patients; only pseudonymized data will be transferred. After receival of this request for randomization of a patient, the third party for randomization will assign a unique trial identifier to the patient at hand and will respond to which treatment arm this patient has been allocated.

As such, the randomization process is concealed for the treating surgeon up until 1 week before surgery. Since these two different techniques may entail different operating room preparations (different retractors, different sutures, etc.), randomization concealment for the treating surgeon is lifted 1 week preoperatively for logistic considerations.

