Be that as it may and potential functional benefits aside, vsAR should at least be able to provide a comparable (or non-inferior) surgical success rate as the transecting technique to be considered a truly valuable alternative. Promising short-term results have been described in single-arm observational studies and are in line with the reported composite success rate of the ICUD [3, 6–10]. However, direct comparisons between vsAR and tAR have only been done in retrospective studies which are strongly biased by the fact that patients who underwent vsAR had shorter follow-up than patients who underwent tAR [11, 12]. Moreover, since vsAR is a more novel technique, one could hypothesize that the performing surgeon is better trained and more experienced in the era of vsAR compared to the earlier in their surgical career, when tAR was the only AR technique.

Considering the above, the aim of this randomized controlled trial is to directly compare vsAR and tAR for both surgical and functional outcomes.

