### Eligibility criteria {10}

Inclusion criteria for participants:
Voluntarily signed written informed consent according to the rules of ICH-GCP (Declaration of Helsinki) and national regulations.Age ≥ 18 years.Male patient.Fit for operation, based on the surgeon’s expert opinion.Isolated short (≤ 3 cm) bulbar urethral stricture confirmed by imaging. Imaging includes at least retrograde urethrography (RUG). In case of equivocal findings, voiding cysto-urethrography (VCUG) and urethroscopy must be added.Patient is able and willing to comply with the postoperative protocol.

Exclusion criteria for participants:
Absence of signed written informed consent.Age < 18 years.Female patients.Transgender patients.Patients unfit for operation.Concomitant urethral strictures at other urethral locations (penile urethra, membranous urethra, prostatic urethra, bladder neck).Urethral strictures > 3 cm.Urethral stricture(s) at other urethral locations (penile urethra, membranous urethra, prostatic urethra, bladder neck).Lichen sclerosus-related strictures.Strictures after failed hypospadias repair.Patients with neurogenic bladder.Shift of technique to augmented urethroplasty or any technique other than AR due to any circumstance. These patients will be logged, but will be excluded (post-hoc) from further analysis within this trial.History of pelvic radiation therapy.Active treatment to enhance erectile function (such as PDE5-inhibitors and intracavernous injections) at the moment of prescreening for inclusion in this trial.Any condition or situation, which, in the investigator’s opinion, puts the patient at significant risk, could confound the study results, or may interfere significantly with the patient’s participation in the study.Patient declares that it will be impossible for him to attend the follow-up consultations.

Eligibility criteria for participating centers:

Only urethral surgeons who state that they are sufficiently capable of performing both vsAR and tAR are allowed to participate in this trial.

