#### Analysis of the primary end-point

Kaplan-Meier curves for FFS will be plotted with the corresponding log-log 80% CIs for vsAR and tAR.

Non-inferiority of vsAR versus tAR in terms of FFS at 24 months will be concluded when the lower limit of the 80% CI for the difference in FFS probability at 24 months does not exceed − 10%. Note that this analysis does not take into account the nesting of patients within centers, which may affect the estimated standard errors.

To take into account the clustering of patients within centers, a marginal Cox proportional hazards model can be fitted (using the cluster function from the “survival” package in R software) which will give a robust estimation of the variance. The lower limit of the 80% CI for the hazard ratio can be transformed into a limit of survival difference at 24 months, assuming an exponential distribution of failure-free survival times [*S*(*t*) = exp.{−*λt*}].

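### The randomisation request names no operating surgeon, yet the arm is released up to a week before surgery, so choice of operator by arm cannot be excluded in centres with several trial surgeons

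*Protocol article*

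**What the plan says.** The allocation procedure is described under Concealment mechanism {16b}. For centres other than Ghent University Hospital, "the local PI will contact the third party for randomization within 1 week before the planned operation". The article gives the content of the request: "patient X who is going to be operated on dd/mm/yyyy". The third party then assigns a trial identifier and replies with the arm. The stated reason for releasing the arm early is operating-room preparation, such as retractors and sutures: "randomization concealment for the treating surgeon is lifted 1 week preoperatively for logistic considerations".

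Three other places bear on who operates:

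- Sequence generation {16a}: "Randomization will be stratified by participating center". Surgeon is not a stratification factor.
- Eligibility criteria {10}: "Only urethral surgeons who state that they are sufficiently capable of performing both vsAR and tAR are allowed to participate in this trial".
- Analysis of the primary end-point: "To take into account the clustering of patients within centers, a marginal Cox proportional hazards model can be fitted". The clustering unit is again the centre.

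The article does not give the number of trial surgeons per centre. It does not say that the operator is recorded or locked before the arm is released, nor that the operator may be changed afterwards.

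**The concern.** In a surgical trial the operator is part of the treatment received. Randomisation balances operators between arms only if the operator is settled before the arm is known. Here the arm is known for up to a week beforehand, and the written request does not tie a surgeon to the patient. In a centre with two or more trial surgeons, ordinary list scheduling with the arm in view could send more vsAR cases to one surgeon and more tAR cases to another. No misconduct is needed.

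Stratifying by centre cannot correct this, because the choice happens within the centre and after randomisation. A robust variance clustered on centre cannot correct it either, because it changes the standard error and not the bias. A difference in failure-free survival (FFS) or erectile function could then partly reflect the operator. If the stronger operators drift towards vsAR, non-inferiority is declared too easily. If they drift towards tAR, a technique that is truly non-inferior may fail.

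**Working it through.** **Inputs from the protocol article.** Sample size {14}: tAR 95.4%, vsAR 95.3%, one-sided alpha 0.10, power 0.80, 41 per arm before drop-out. Objectives {7}: margin 10 points. Standard normal quantiles: z(0.90) = 1.2816 and z(0.80) = 0.8416.

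**Step 1: reproduce the plan's figure.**

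n per arm = [pT(1−pT) + pV(1−pV)] × (z(0.90) + z(0.80))² / (0.10 − (pT − pV))²

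= [0.954×0.046 + 0.953×0.047] × (2.1232)² / (0.099)² = 40.8, rounded up to 41. This agrees with the article.

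**Step 2: chance of declaring non-inferiority.** With the same approximation,

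P = Φ[(0.10 − (pT − pV))/SE − 1.2816], where SE = √{[pT(1−pT) + pV(1−pV)]/41}.

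At the planning values SE = 0.0465 and P = Φ(0.847) = 0.80, which matches the stated power.

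**Step 3: assumed operator shift.** The article has no surgeon-level data, so these inputs are assumptions. The net shift is the difference between arms in the share of cases done by the better operators, multiplied by the gap in 24-month failure risk between operator groups:

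- 20-point imbalance × 5-point gap: 0.20 × 0.05 = 1 point
- 30-point imbalance × 10-point gap: 0.30 × 0.10 = 3 points

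The whole shift is placed on the observed vsAR rate, with tAR held at 95.4%.

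**Step 4a: shift favours vsAR, true vsAR rate 85.4% (a 10-point deficit).**

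| Shift | Apparent vsAR FFS | SE | P(declare non-inferiority) |
|---|---|---|---|
| 0 | 85.4% | 0.0641 | Φ(−1.282) = 10.0% |
| 1 point | 86.4% | 0.0627 | Φ(−1.122) = 13.1% |
| 3 points | 88.4% | 0.0598 | Φ(−0.780) = 21.8% |

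**Step 4b: shift favours tAR, true vsAR rate 95.3%.**

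| Shift | Apparent vsAR FFS | SE | Power |
|---|---|---|---|
| 0 | 95.3% | 0.0465 | Φ(0.847) = 80.2% |
| 1 point | 94.3% | 0.0488 | Φ(0.542) = 70.6% |
| 3 points | 92.3% | 0.0529 | Φ(0.022) = 50.9% |

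**Step 5: are the assumed inputs possible?** With a 30-point imbalance favouring vsAR, the better operators do at most 70% of tAR cases, so the others do at least 30%. With a 10-point gap, tAR failure is then at least 0.30 × 10 = 3.0%, which fits within the 4.6% used. The 20 × 5 case needs at least 0.20 × 5 = 1.0% and also fits.

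**The case against.** The strongest reply is that the gap is read from silence. The article speaks of the treating surgeon as someone already attached to the patient, the operation already has a date, and early release is justified by equipment and not by surgeon assignment. A condensed article may also leave operator listing to site instructions. This stands in part. A reader might infer that the operator is in fact left open, or is chosen by arm, and the documents do not show that. What remains is that the article does set out the request procedure, including its content, channel and timing, and the request as worded contains no operator. A usual surgeon is not a binding one.

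A second reply is that every trial surgeon must state that he can perform both techniques. That is a real safeguard and limits the confounding. It is self-declared and sets no case minimum, so it gives a floor and does not make surgeons equal.

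Third, a reader might infer that the trial repeats a bias it criticises, since Background and rationale {6a} says "one could hypothesize that the performing surgeon is better trained and more experienced in the era of vsAR". The comparison there is with earlier in the same surgeons' careers, when only tAR was done. That is a calendar-time learning effect, which concurrent randomisation removes. Choice between colleagues after allocation is a different route, and the introduction does not mention it.

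Fourth, the size rests on assumption. That is correct. It is also tempting to assume more, such as a 50-point imbalance with a 10-point gap. That case contradicts the planning rate: the better operators would do at most half of the tAR cases, so tAR failure would be at least 0.50 × 10 = 5.0%, above the 4.6% used.

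**Conclusion.** The point holds in a limited form. The written procedure releases the arm up to a week before surgery on a request without an operator, and neither stratification nor the clustering adjustment reaches the surgeon. Choice of operator by arm therefore cannot be excluded where a centre has more than one trial surgeon. The documents do not show that it happens, or in which direction it would work.

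Under assumed net shifts of 1 to 3 points, with 41 per arm and one-sided alpha 0.10, the false-positive rate at a true 10-point deficit rises from 10% to about 13% to 22%, or power falls from about 80% to about 71% to 51%. Only the conversion from shift to error rate is calculated. The shifts are not from the documents, and in single-operator centres they are zero. This is a worthwhile, cheap improvement to the procedure and does not affect the sample size.

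**What to change.** In Concealment mechanism {16b}:

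1. Add a coded operating-surgeon field to the randomisation request, alongside the patient and the date. The third party logs it before releasing the arm.
2. State that the named surgeon operates whichever arm is drawn.
3. Record any later change of operator with its reason, and report operator by arm.
4. Apply this at every centre. The request is worded only for centres other than Ghent University Hospital, although Implementation {16c} describes third-party allocation without exempting any centre.

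The cost is one extra field in a telephone or e-mail request and a few added sentences in the protocol. The downside is slightly less freedom to swap operators in the final week. No extra patients, visits or procedures are needed, and the arm can still be released early enough to prepare the operating room.
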